### **Adverse Events and Serious Adverse Events**

Adverse events (AEs) and serious adverse events (SAEs) will be collected every 2 weeks and whenever the study team learns of an event between the biweekly assessments during the intervention period. These will also be collected at 6- and 12-month follow-up, during which patients will be asked to report all SAE/AEs since the last assessment. The pre-specified serious adverse events include – death, hospitalization/ER visit, bleeding requiring transfusion or hospitalization (due to possible selective serotonin reuptake inhibitor mediated reduction in platelet aggregation), medication overdose requiring ER visit/hospitalization (as determined by review of medical records) and acute suicidal intent. Relatedness of AE/SAEs with study interventions, especially with medications prescribed for symptom management, will be reviewed by external Adverse Events committee and reported.

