| Study Intervention                                                                                               | Technology Assisted stepped Collaborative Care (TĀCcare)
Technology Assisted Health Education Attention Control                                                                                                                                                                                                                                                                                                                                                                                                                                                                                                                                                                |
| Intervention Duration (per participant)                                                                          | TĀCcare: 12 weekly sessions
Control: 6 sessions over 12 weeks                                                                                                                                                                                                                                                                                                                                                                                                                                                                                                                                                                                                                  |
| Follow-up Duration (per participant)                                                                             | 12 months                                                                                                                                                                                                                                                                                                                                                                                                                                                                                                                                                                                                                                                                         |

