### **Treatment Intervention Study Arms**

**A) Technology Assisted Stepped Collaborative Care Intervention (TĀCcare):** Patients randomized to the intervention arm will receive a stepped-care approach of pharmacotherapy and/or CBT for a 12-week period. The intervention will target one or more symptoms based on patients' report of clinical levels of each symptom and patient preference. A local care coordinator at each clinical site will be assigned to each patient. During weekly online video-conferencing sessions, care coordinators will engage the patient actively, encourage and monitor treatment adherence, and assess response and side-effects. Both clinical sites have secure and established telemedicine portals that are routinely used for clinical care and research (Vidyo at University of Pittsburgh and Echo Zoom at University of New Mexico). These live video-based face-to-face sessions will be conducted during one of the thrice weekly HD sessions at the dialysis unit with optional privacy screen. For each dialysis unit, the study will provide iPads, portable secure Wi-fi hotspot, wireless headphones and microphones. Similar to our pilot study (manuscript in preparation), these devices will be pre-programmed to ensure patient's ease and independence of use with minimal training, even among the elderly or those with limited technology experience, thus causing minimal additional burden for the dialysis staff. If there are any medical emergencies during the HD session, the video-based session will be cancelled and rescheduled once the patient is clinically stable. If the patients have the needed technology at home, they will have the option of doing these video-conferencing sessions at home.

**B) Stepped Approach to Individualize Treatment:** Treatment options include pharmacotherapy or CBT or both, based on patient's symptom severity and preference. As the causes for fatigue in these patients are multifactorial, fatigue management algorithm will include assessment of depressive symptoms, sleep quality, pain, physical inactivity and medication side-effects and these contributing factors will be addressed as needed. In addition, we will ensure that dialysis dose and hemoglobin are in target ranges.

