**D) Pharmacotherapy:** The research team will follow an evidence-based protocol to recommend whether a medication should be initiated, changed or intensified. For pain management we will use the World Health Organization 3-step analgesic ladder modified to adjust medication dosage for HD. Such an approach has also been developed by the Mid-Atlantic Renal and Kidney End-of-Life Coalitions through support by the Center of Medicare and Medicaid Services. This approach has been successfully used in HD patients and has been highly efficacious in controlling pain in over 95% of participants. Pain medication algorithms will be based on whether the patient has neuropathic pain, nociceptive pain or both. Pharmacological treatment of depression will be based on efficacy and safety evidence in HD patients and dose adjustment for HD will be recommended as appropriate. The research team including nephrologists and internist with symptom management expertise, along with clinical psychologist will make medication recommendations. These providers have training and experience with pharmacotherapy for symptom management. The recommendations will be conveyed to the patients' primary care provider (PCP) and/or nephrologist by the care coordinator, who will also monitor anti-depressant and analgesic medication adherence and side effects during weekly sessions. . Once the patient's PCP and/or nephrologist approve of the medication change, the care coordinator will facilitate implementation of the treatment by communicating and coordinating with the dialysis team and pharmacy if needed, so as to minimize burden on dialysis staff. The research team will not prescribe or provide any medications. To ensure that patient's PCP and/or nephrologist prescribe the recommended by the study medications, we will conduct regular educational and outreach meetings, and will communicate regularly with the physicians throughout the study period.

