**E) Collaborative Care:** An important aspect of TĀCcare is the integration of care provided as part of research with the patient's routine clinical care. The care coordinators will serve as a liaison between the patient and other health care professionals within the patients' medical team. This is important for providing a multi-disciplinary approach to the patient's physical and mental health, for aligning symptom management with the patient's overall plan of care, and for ensuring patient acceptance and adherence to the study team's recommendations. To facilitate such collaboration, the care coordinator will communicate (via email or phone or personal meeting) with the dialysis team at least monthly and whenever medication changes are recommended; participate in monthly dialysis care plan meetings whenever possible, and will discuss any pertinent issues with the dialysis care team ( nephrologist, nurses or social worker) at least monthly. We will record the type and frequency of communication with the care team."

The care coordinator will also participate in clinical dialysis care plan meetings and will provide recommendations as appropriate. The care coordinators are Master's level behavioral therapists who received specific training in cultural competence on HD-specific issues and will work closely under the supervision of a local study psychologist.

**Technology Assisted Health Education Attention Control:** Patients randomized to this study group will be provided with iPads during HD (same as the intervention group) and will have weekly sessions to match the frequency of contact in the intervention group. To match the attention and expectations of patients in this group, a care coordinator will use video-conferencing to deliver health education. Although weekly sessions with care coordinator would have been ideal, this is not financially feasible. Thus, these sessions will alternate with sessions in which access to educational videos and online educational material from the National Kidney Foundation (NKF; [www.nkf.org](http://www.nkf.org)) will be provided. Topics relevant to ESRD such as transplantation, heart health, immunizations and age appropriate cancer screening, etc. will be covered.

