**Measuring Selected Pro/anti-inflammatory Cytokines:** Selected cytokines (*high sensitivity C - reactive protein; hs-CRP, Interleukin; IL-6, IL-10 and Tumor Necrosis Factor; TNF- $\alpha$* ) were chosen based on their reported associations with the outcomes of interest. All blood samples will be shipped at regular intervals and cytokine measurements will be performed centrally at the University of Pittsburgh. We will collect 10ml of blood drawn pre-dialysis at baseline, post 12-week intervention and at 6-month follow-up. Serum will be aliquoted within 4 hours of the blood draw, shipped on dry ice and stored at -80°C for batch analysis. Cytokine levels will be measuring using Luminex™ bead-set (Millipore Corporation, Billerica MA and Luminex™ 100 IS apparatus, Austin TX) in accordance with the manufacturer's instructions using standardized validated assays and operating procedures.

**Descriptors and Potential Covariates:** Baseline patient data collection will include socio-demographic data such as age, gender, race, ethnicity, education, marital and employment status, household income, etc. The patient's clinical characteristic such as years on dialysis, comorbid conditions, concomitant medications, etc.

along with data on hospitalizations, mortality and transplantation will be obtained from patient interviews and medical chart abstraction. Routine monthly laboratory assessment done by the dialysis clinics will be extracted.

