### **Side Effects and Tolerability Data**

The side effects and tolerability data will be collected every 2 weeks in both study arms. The side effects will be collected using the modified Patient Related Inventory of Side Effects (PRISE) questionnaire. This 20-item questionnaire asks about occurrence and tolerability of 20 common side effects. We will also add an open-ended question to record any other symptoms that patients might have. Although this questionnaire was developed and used to assess side effects of antidepressant medications, we will use the same questionnaire for assessing side effects and tolerability of pain medications because of significant overlap in the commonly reported side effects of these medications.

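### Recording adverse events as the team learns of them gives TĀCcare more chances of detection than control, so a comparison of all recorded events risks ascertainment bias, mainly for non-serious events

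*Protocol*

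**What the plan says.** The section Adverse Events and Serious Adverse Events sets two routes for the intervention period: events "will be collected every 2 weeks and whenever the study team learns of an event between the biweekly assessments during the intervention period". At 6 and 12 months there are follow-up assessments "during which patients will be asked to report all SAE/AEs since the last assessment". None of this is arm-specific.

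Contact with the study team does differ by arm:

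- **TĀCcare.** The Synopsis gives 12 weekly sessions. Under Treatment Intervention Study Arms, part A, "care coordinators will engage the patient actively, encourage and monitor treatment adherence, and assess response and side-effects". Part D has the coordinator convey medication recommendations, "who will also monitor anti-depressant and analgesic medication adherence and side effects during weekly sessions". Part E makes the coordinator a liaison who communicates with the dialysis team at least monthly and whenever a medication change is recommended, and who "will discuss any pertinent issues with the dialysis care team".
- **Control.** The Synopsis gives "Control: 6 sessions over 12 weeks". The attention-control paragraph describes live health education alternating with videos and online material. It describes no side-effect enquiry and no liaison with dialysis staff.

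Two other sources are arm-neutral. Side Effects and Tolerability Data states: "The side effects and tolerability data will be collected every 2 weeks in both study arms", using a 20-item questionnaire (PRISE) with an added open question. Descriptors and Potential Covariates lists clinical characteristics "along with data on hospitalizations, mortality and transplantation will be obtained from patient interviews and medical chart abstraction".

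**The concern.** Scheduled enquiry is balanced, but the second route is only as balanced as the contact that feeds it. A site that follows the rule exactly has more occasions to hear of an event in a TĀCcare patient than of the same event in a control patient. The TĀCcare coordinator has twice as many live sessions, is tasked with asking about side effects, and talks to the staff who see the patient at dialysis.

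The study recommends antidepressants and analgesics in TĀCcare, so event frequencies by arm are what a DSMB or reader will look at for harm. If all recorded events are compared, some excess in TĀCcare could reflect closer observation. If the source of an event is not noted when it is logged, no later analysis can separate the two routes.

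**Working it through.** The protocol states no event rate or capture rate, so there is no figure to reproduce. The check has two parts.

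**1. Opportunities for detection in the 12 weeks**

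| Route | TĀCcare | Control |
|---|---|---|
| Scheduled 2-weekly event collection | 12/2 = about 6 | about 6 |
| PRISE | every 2 weeks | every 2 weeks |
| Live coordinator sessions | 12 | 6 |
| Side-effect enquiry in those sessions | weekly | none described |
| Dialysis-team liaison | at least monthly | none described |
| Chart abstraction of hospitalization and death | yes | yes |

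The rows on live sessions, enquiry and liaison feed the second route, and all of them favour detection in TĀCcare.

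**2. Illustration of size (all capture rates are assumptions)**

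Let true event rates be equal. Let c be the share of events caught by scheduled collection in both arms. Let e_T and e_C be the shares of the missed events caught by other contacts in TĀCcare and control. Then

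recorded ratio = [c + (1 − c)·e_T] / [c + (1 − c)·e_C].

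| c | e_T | e_C | Ratio, TĀCcare to control |
|---|---|---|---|
| 1.00 | any | any | 1.00 |
| 0.95 | 0.25 to 0.75 | 0 | 0.9625/0.95 = 1.01 to 0.9875/0.95 = 1.04 |
| 0.90 | 0.25 to 0.75 | 0 | 0.925/0.90 = 1.03 to 0.975/0.90 = 1.08 |
| 0.80 | 0.25 to 0.75 | 0 | 0.85/0.80 = 1.06 to 0.95/0.80 = 1.19 |
| 0.70 | 0.50 | 0.25 to 0 | 0.85/0.775 = 1.10 to 0.85/0.70 = 1.21 |
| 0.50 | 0.50 | 0.25 to 0 | 0.75/0.625 = 1.20 to 0.75/0.50 = 1.50 |

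The same inputs can be applied to the proportion of patients with at least one event. Assume a true 50% in each arm, the target of 160 split as 80 per arm, e_C = 0, and a simple two-proportion comparison (which the protocol does not specify). At c = 0.80 the recorded proportions are 42.5% to 47.5% against 40%. The chance of a nominally significant excess in TĀCcare is then about 5% to 16%, against a nominal 2.5%. At c = 0.95 and e_T = 0.50 it is about 3.6%.

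**The case against.** The strongest reply is that the protocol already contains a like-for-like safety comparison. PRISE runs in both arms on the same schedule, and event collection does too. An event picked up between assessments in TĀCcare can be reported by a control patient at the next assessment, at most two weeks later, so the second route may change timing more than capture. Hospitalizations and deaths are also abstracted from charts without distinction by arm, and control patients do have six live sessions in which an event may come up. All of this stands, and it confines the concern mainly to non-serious events and to serious events known only by report. Acute suicidal intent without admission could be one of these. ER visits, which are on the pre-specified list of serious events, are not named in the chart-abstraction sentence.

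Two parts of the reply do not remove the point. Symmetric scheduled collection cancels the difference only if recall at those assessments is complete. The external committee reviews the relatedness of events already captured, so it cannot correct unequal capture.

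It can also be said that counting and comparing events belongs to an analysis plan that is not shown. That is fair for the tables. The collection rule is fixed in this protocol, however, and the source has to be noted when the event is recorded.

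A reader might infer that the safety comparison is biased outright, or that a true excess could never be told apart from closer observation. The document does not support either reading. Nowhere does it say that both routes feed a single count compared between arms, and PRISE gives a balanced comparison of common side effects.

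**Conclusion.** The point holds as a risk of ascertainment bias in a comparison of all recorded events. The expected direction is more events in TĀCcare. Its size cannot be known from the document. On the assumed inputs it is close to nil if scheduled capture is nearly complete (ratio 1.01 to 1.08 at 90-95%), and material if capture is incomplete (about 1.1 to 1.5 at 50-70%). The upper end needs half of all events to be missed at scheduled assessments and control contacts to recover none of them. The conclusion rests on the control arm having no side-effect enquiry or dialysis-team liaison beyond what is described, and on event source not already being captured on a form that is not shown. The primary efficacy analysis is unaffected. This is a cheap improvement.

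**What to change.** 1. Add a field to the event form for source: scheduled assessment or learned otherwise.
2. At each 2-weekly assessment and at 6 and 12 months, ask both arms the same questions about all events since the last assessment, including those the team already knows of. Otherwise a TĀCcare patient who has told the coordinator may not repeat the event, and the scheduled count would under-record that arm.
3. Make the main between-arm safety comparison from three sources: events elicited at scheduled assessments, PRISE, and deaths and hospitalizations from chart abstraction done identically in both arms. State whether abstraction covers ER visits.
4. Beside it, show the comparison of all events, including those learned otherwise and every pre-specified serious event such as acute suicidal intent. Leaving these out altogether could hide a real signal.

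The cost is one form field, a second safety table and somewhat lower counts in the main comparison. If ER visits are to be abstracted, that adds some chart work. Events continue to be recorded and reported whenever the team learns of them.

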### **Side Effects and Tolerability Data**

The side effects and tolerability data will be collected every 2 weeks in both study arms. The side effects will be collected using the modified Patient Related Inventory of Side Effects (PRISE) questionnaire. This 20-item questionnaire asks about occurrence and tolerability of 20 common side effects. We will also add an open-ended question to record any other symptoms that patients might have. Although this questionnaire was developed and used to assess side effects of antidepressant medications, we will use the same questionnaire for assessing side effects and tolerability of pain medications because of significant overlap in the commonly reported side effects of these medications.

### **Outcomes**

The primary outcome of the trial is clinically meaningful change (effect size 0.6) in depression, pain or fatigue as ascertained blindly by the *Beck Depression Inventory-II (BDI-II)*, *Functional Assessment of Chronic Illness Therapy Fatigue (FACIT-F)* and *Brief Pain Inventory (BPI) Short form* questionnaires respectively, after a 12-week intervention as compared to control arm. We used effect size (ES) i.e. standardized mean difference instead of raw mean difference as our outcome as this places the emphasis on the most important aspect of an intervention - the size of the effect - rather than its statistical significance. Moreover, in our study the 3 symptoms will be measured using different instruments with varying scales, and ES facilitates standardizing the observed changes in these symptoms. By quantifying the magnitude of the difference between the two study groups, ES gives a more complete and clinically relevant picture of health status change. Cohen's d effect size of 0.6 is considered moderate size and is likely to translate into clinically meaningful improvements in the symptoms. Secondary patient-reported outcomes include change in HRQOL and EMA-measured composite score of fatigue, sleepiness and mood after 12-week intervention. Additional secondary outcomes include adherence to medications, diet and HD treatments; as well as changes in levels of biomarkers of inflammation.

### **Original Statistical Analysis Plan**

**Sample Size and Power:** We powered our study to detect a clinically meaningful difference in our primary outcomes -- depression, pain, or fatigue -- for Aim 1 at 12 weeks while considering feasibility of subject recruitment. Since there is no validated composite endpoint consisting of the 3 outcomes, we will test the effect of TASCCI on each of the outcomes. We calculated power controlling for False Discovery Rate (FDR) of 5% using the Benjamini-Hochberg correction. To be more conservative, (1) we used a two-sided two-sample t-test in the calculations and (2) assumed that the intervention has a true effect on exactly one endpoint.

Our primary analysis will compare groups at 12 weeks using contrast from a mixed model that includes all time points (baseline, 12 weeks, 6 months, and 12 months). By using all available longitudinal data, our primary analytical approach would be more efficient than t-test and provide greater power to detect differences. We will also have increased power if the intervention has real effect on more than one endpoint.

The projected total sample size is 150, or 75 per group. After accounting for the estimated 10% lost-to-follow-up, the effective total sample size is 136. For this sample size, Table 1 shows the estimated power for a range of effect sizes (standardized mean difference) with and without adjusting for FDR using PASS 13 (NCSS, LLC, Kaysville, UT)

**Table 1:** Estimated power for total sample size of  $N = 136$  for a range of effect sizes with and without adjusting for a 5% false discovery rate (FDR).

| Effect Size
(Standardized Mean
Difference) | FDR-
unadjusted | FDR-adjusted |             |
|--------------------------------------------------|--------------------|--------------|-------------|
|                                                  |                    | 3 endpoints  | 4 endpoints |
| 0.4                                              | 64%                | 40%          | 32%         |
| 0.5                                              | 82%                | 70%          | 63%         |
| 0.6                                       | 93%         | 88%   | 85%  |
| 0.7                                              | 98%                | 96%          | 95%         |
| 0.8                                              | 100%               | 99%          | 99%         |

Thus, our sample size provides 88% power to detect an effect size of 0.6 controlling for 5% FDR for 3 endpoints assuming a true difference exists in 1 out of 3 endpoints. If differences exist on 2 of 3 endpoints, we will have 89% power to detect an effect size of 0.5. The detectable effect size is consistent with what we observed in our study of SCCI in cancer patients (effect size was 0.7 for depression, 0.6 for pain and 0.3 for fatigue, respectively).

In May 2020, the sample size was increased to 160 participants per DSMB recommendations given a higher observed attrition rate (14%).

**General Statistical Approach:** Distributions of baseline characteristics will be compared between the groups to assess effectiveness of randomization, and statistical differences will be accounted for as covariate in secondary adjusted analyses. All primary analyses will be adjusted for site, age, and comorbidity (design variables) as well as sex and unadjusted analyses will also be reported per CONSORT recommendations. The stratification variables are potentially prognostic of the outcomes, which likely will make the adjusted analyses more efficient than unadjusted. The primary analyses will use the 'intent-to-treat' approach in which subjects are analyzed in their assigned group, regardless of treatment adherence, withdrawal or deviation from protocol. General linear mixed models (GLMM) will be used for inferential analyses of primary and secondary outcomes. Unless otherwise specified, all tests will be conducted using two sided 5% level of significance. We will report our findings according to the CONSORT guidelines.

**Preliminary Analyses** will focus on data checks for completeness and accuracy and address any issues with data quality. The preliminary exploration of the data will be used to: 1) examine univariate and bivariate distributions; 2) identify any imbalances between treatment groups on baseline characteristics; 3) investigate the magnitude of the associations between the dependent variables and the potential covariates; 4) verify the statistical assumptions of the planned primary analyses. If assumptions are violated, then alternative procedures such as data transformations or more robust statistical methods will be considered.

